## Abstract

**Background:**

Proactive palliative care is not yet common practice for patients with COPD. Important barriers are the identification of patients with a poor prognosis and the organization of proactive palliative care dedicated to the COPD patient. Recently a set of indicators has been developed to identify those patients with COPD hospitalized for an acute exacerbation who are at risk for post-discharge mortality. Only after identification of these patients with poor prognosis a multi disciplinary approach to proactive palliative care with support of a specialized palliative care team can be initiated.

**Methods/Design:**

The PROLONG study is a prospective cluster controlled trial in which 6 hospitals will participate. Three hospitals are selected for the intervention condition based on the presence of a specialized palliative care team. The study population consists of patients with COPD and their main informal caregivers. Patients will be included during hospitalization for an acute exacerbation. All patients in the study receive standard care (usual care). Besides, patients in the intervention condition who meet two or more criteria of the set of indicators for proactive palliative care will have additionally regular consultations with a specialized palliative care team. The objectives of the PROLONG study are: 1) to assess the discriminating power of the proposed set of indicators (indicator study) and 2) to assess the effects of proactive palliative care for qualifying patients with COPD on the wellbeing of these patients and their informal caregivers (intervention study). The primary outcome measure of the indicator study is time to death for any cause. The primary outcome measure of the intervention study is the change in quality of life measured by the St George Respiratory Questionnaire (SGRQ) three months after inclusion.

**Discussion:**

The PROLONG study may lead to better understanding of the conditions to start and the effectiveness of proactive palliative care for patients with COPD. Innovative aspects of the PROLONG study are the use of a set of indicators for proactive palliative care, the active involvement of a specialized palliative care team and the use of a patient-tailored proactive palliative care plan.

**Trial registration:**

Netherlands Trial Register (NTR): NTR4037

## Background

In 2002 the World Health Organization (WHO) introduced a new definition of palliative care. They emphasized in this definition the importance of early identification and impeccable assessment and treatment of pain and other problems, physical, psychosocial and spiritual in order to prevent and relief suffering [1]. This means that palliative care is not limited to the terminal phase and can be delivered beside curative care to patients with a life-threatening illness. It implicates that palliative care is not only restricted to reactive symptom relief. By anticipating on expected disease scenario’s and the specific needs and wishes of a patient, problems can be prevented and hence quality of life improves. The clinical use of this proactive palliative care is growing in care for patients with cancer. Still a proactive approach is not very common for patients with Chronic Obstructive Pulmonary Disease (COPD), even though the symptoms that occur in the end stage of COPD are as severe or even worse than in the final stage of lung cancer [2,3]. Both groups of patients prefer a treatment with the emphasis on comfort instead of life prolongation, but to patients with COPD this is offered less frequently [4]. For instance patients with COPD receive less opioids and benzodiazepines than patients with lung cancer for their dyspnea complaints [5], and they die more often at an Intensive Care Unit (ICU) [6].

Several barriers are described with respect to offering proactive palliative care to patients with COPD [7]. A first important barrier is the identification of patients with COPD who can benefit from proactive palliative care, as it is difficult to predict the remaining length of survival of these patients [8]. For that reason, recognizing the appropriate time to start proactive palliative care may not be obvious for clinicians. A second important barrier is the organization of proactive palliative care for COPD patients. The majority of hospitals in Europe have no formalized approach regarding palliative care issues for patients with COPD: these patients have less universal access to specialist palliative care services than those with malignant lung diseases [9-11].

In general, an important problem in the transition or referral to palliative care services is that the term “palliative care” is often associated with terminal or end stage care only. This can be an impediment to early implementation of proactive palliative care as proposed by the WHO. Especially for patients with COPD who do not perceive COPD as an illness that disrupts life [12]. Hence the term ‘supportive care’ may be a term more conducive to referral and may facilitate integration between curative care and palliative care for patients with COPD [13-15]. Therefore, in this study we will speak of supportive care in contact with participating patients with COPD.

### Identification of patients with COPD for proactive palliative care

COPD illustrates the ‘organ failure’ end-of-life trajectory in which a gradual decline is punctuated by acute severe exacerbations, any one of which may be fatal [16,17]. The patient may survive the majority of these exacerbations as long as he shows resilience and rebounds to (at least part of) his former condition. As it is unclear which exacerbation will be fatal, death may seem to occur suddenly [18] (Figure 1).

**Figure 1 F1:**
[figure not shown]
COPD disease trajectory.

This uncertain prognosis makes it difficult for clinicians to initiate discussions about palliative care and end–of–life care planning [19,20]. In stable COPD, population models of 6 month survival do exist but they are of limited value to predict death for individual patients [21]. It is therefore proposed to address proactive palliative care at certain milestones in the course of the disease [22], such as the occurrence of an acute exacerbation COPD (AECOPD) [20]. An AECOPD is defined as ‘an acute worsening of the patient’s condition from the stable state, which is sustained and may warrant the patient to seek additional treatment’ [23]. Exacerbations cluster in time with a high risk of recurrence within 8 weeks of recovery [24], and show an increasing frequency as the disease progresses [25]. Recovery after an AECOPD is often to a suboptimal condition as before the exacerbation and after each exacerbation more care may be required to support the patient and the family. Therefore each admission to the hospital for an AECOPD creates an opportunity to identify patients at high risk of subsequent readmission or post-discharge mortality and hence who can benefit from a proactive palliative care approach. Several studies focused on the identification of predictive factors associated with hospital readmission or mortality for patients with an AECOPD. The findings of these studies are summarized in a recent review [26]. One of the conclusions is that in-hospital mortality is related to the patient’s acute physiological state and to the development of acute comorbidity while post-discharge mortality particularly reflects the severity of the underlying COPD, as well as concomitant specific comorbidities. Important factors influencing the frequency of readmission include functional limitation and poor health-related quality of life. A profile emerges of the types of patients hospitalized for an AECOPD at high risk of subsequent readmission or post-discharge mortality [19].

In accordance with these findings and based on existing literature [19,26-29] we developed a set of indicators for lung specialists to improve the identification of patients hospitalized for an AECOPD for whom proactive palliative care might be beneficial. We hypothesize that the presence of two or more of the following indicators (or prognostic conditions) should be a reason to start proactive palliative care: 1) hypoxaemia or hypercapnia at discharge; 2) treatment of the exacerbation with Non Invasive Ventilation (NIV); 3) patient needs professional home care service for personal care after discharge; 4) a negative answer to the surprise question: ‘Would I (as lung specialist) be surprised if this patient would have a subsequent readmission for AECOPD within 8 weeks and/or would die in the next year?; 5) the diagnosis of a severe comorbidity such as: a) non-curable malignity or b) cor pulmonale (proven or non proven) or c) proven Chronic Heart Failure (CHF) or d) diabetes mellitus with neuropathy or e) renal failure, clearance < 40 Glomerular Filtration Rate (GFR); 6) Clinical COPD Questionnaire (CCQ) total, day version ≥ 3; 7) Medical Research Council dyspnea questionnaire (MRC dyspnea) = 5; 8) Forced Expiratory Volume in 1 second (FEV1), measured before AECOPD < 30% of predicted; 9) Body Mass Index (BMI) < 21 or unplanned weight loss (> 10% weight loss in last 6 months or > 5% in last month); 10) previous hospital admissions for AECOPD (last 2 years ≥ 2 and/or last year ≥ 1); 11) Age > 70 years.

In this study the discriminating power of this set of indicators will be examined. We hypothesize that the set of indicators can predict readmission within 8 weeks and/or death within 1 year for patients hospitalized for an AECOPD.

### Organization of proactive palliative care for patients with COPD

Provision of palliative care for patients with COPD in Europe is variable, and overall very small [11]. The majority of hospitals in Europe do not have a formalized approach to palliative care issues for patients with chronic lung disease. Besides patients with advanced non-malignant respiratory disease have less universal access to specialist palliative care services than those with malignant lung disease [9-11]. In a survey performed in the UK, the minority of hospital units had a formal referral pathway for palliative care and only about 13% had a policy of initiating end-of-life discussions with appropriate patients [30]. Although variation in care may be influenced by many factors including availability, access and reimbursement issues, such geographic variations suggest a lack of consensus concerning the best approach to palliative care for patients with COPD [19].

Therefore, recent studies have focused on the best approach and content of palliative care for patients with COPD. It is suggested to start palliative care early beside curative care [31]. Furthermore, good proactive palliative care should at least consist of: 1) a standardized inventory of current and future care needs and a structured organization of proactive palliative care; 2) advance care planning (ACP), which involves the patient (−family)-clinician communication about end-of-life care and the completion of advanced directives [20]. Important components of ACP are discussions about the expected course of the disease and prognosis and counseling concerning preferences for care at the end of life, including spiritual care [19]; 3) development and implementation of a patient-tailored proactive palliative care plan. There are several problems from the patient as well as from the clinician perspective when it comes to satisfactory implementation of ACP and a patient-tailored proactive palliative care plan [7]. First, there are clinician and patient related barriers to discuss ACP [32]. Patients for instance avoid ACP discussions out of fear of suboptimal treatment in case of emergencies while clinicians are concerned that early ACP will take away patients’ hope [20]. Discussions about ACP are therefore unlikely to occur and when they do occur they are likely to be of poor quality [19]. Second, not all clinicians have a special interest in or are qualified to perform proactive palliative care. Finally, delivering proactive palliative care beside curative care for patients with COPD may increase the workload and clinicians may be faced with shortage of time [7]. In order to overcome these problems it is suggested that a multidisciplinary approach to proactive palliative care with better access to specialist palliative care services will help patients with COPD navigate through the continuum of chronic disease management and will improve quality of end-of-life care [7,10].

Unfortunately, no research data is available on the beneficial effects of a multidisciplinary approach to proactive palliative care for patients with COPD in terms of reducing the healthcare utilization (for example, hospital readmission) or improving quality of life. However, in a study in male patients predominantly diagnosed with cancer but also with cardiovascular and pulmonary diseases, the benefits of palliative care provision appeared effective compared with usual care [33]. Patients receiving palliative care were less likely to be admitted to the ICU during hospitalization, had lower inpatient cost per day and received better medical care provision compared to usual care patients. Hence proactive palliative care may avoid admission to the ICU for patients with COPD and may help to reduce health care costs. More research data is available concerning the beneficial effects of an early introduction of palliative care for patients with cancer. In a recent study [34] the effect of introducing early palliative care among patients diagnosed with metastatic non-small-cell lung cancer was examined in a randomized controlled trial (RCT). As compared to patients receiving standard care, patients receiving early palliative care had a better quality of life, less depressive symptoms, less aggressive care at the end of life and longer survival.

In the present study the effects of proactive palliative care performed by a specialized palliative care team for patients with COPD on the wellbeing of these patients and their informal caregivers will be examined. We hypothesize that proactive palliative care for patients with COPD will: increase the quality of life of these patients, decrease the number and length of acute hospital admissions and ICU admissions, prolong survival of these patients, decrease the number of patients that die in the ICU, and decrease the level of overburdening of their informal caregivers.

## Methods/Design

### Objectives

The PROLONG study exists of two parts, an indicator study and an intervention study, each with its own primary and secondary objectives:

#### Objectives indicator study

1. The primary objective is to assess the discriminating power of a set of indicators that indicates the start of proactive palliative care for patients with COPD.

2. The secondary objective is to examine to what extend individual indicators (or clusters) indicative are for the need of proactive palliative care.

#### Objectives intervention study

1. The primary objective is to assess the effects of proactive palliative care delivered by a specialized palliative care team on the wellbeing of patients with COPD with poor prognosis and their informal caregivers.

2. The secondary objective: is to assess survival rate in COPD patients with proactive palliative care integrated with standard care versus standard care only.

### Study design

The study consists of a controlled trial (assessment) with hospital as cluster, with a pre- and a post-test assessment. In total 6 hospitals will participate, 3 hospitals in the intervention condition and 3 hospitals in the control condition. Hospitals are selected for the intervention condition based on the presence of a specialized palliative care team. In the hospitals in the control condition standard care (usual care) will be delivered to patients with COPD by their treating lung specialists. In the hospitals in the intervention condition all patients with COPD will receive standard care by their treating lung specialist and those patients that are indicated for proactive palliative care by our set of indicators will also be supported by a specialized palliative care team on a regular base. Baseline measurements of the intervention study will be assessed from all participating patients during hospitalization for AECOPD before start of the intervention. Follow-up measurements will take place every three months, starting from the moment of discharge for a period of one year or until death. The primary outcome measure of the indicator study is time to death for any cause. The primary outcome measure of the intervention study is the change in quality of life measured by the St George Respiratory Questionnaire (SGRQ) at three month after baseline. As pre-test assessment, data will be obtained from the databases of the participating hospitals over a one year period preceding the assessment. These data on hospital-level are necessary to be able to compare hospitals at baseline. As post-test assessment, retrospectively the medical files of all participating patients will be examined over the assessment period. The assessment will take 18 month; 6 month for inclusion and 12 months for follow-up. The post-test assessment will be performed in the 3 months after the assessment.

### Study population

Patients with a hospital admission for AECOPD will be invited to participate. If they agree to participate, their main informal caregiver will also be asked to participate.

#### Inclusion criteria

In order to be eligible to participate, a patient must meet the following criteria:

● Being admitted to the hospital for AECOPD, and

● Aged 18 years or older.

#### Exclusion criteria

A patient that meets any of the following criteria will be excluded from participation:

● Not speaking the Dutch language, or

● Having severe cognitive disorders, or

● At moment of inclusion being treated by a specialized palliative care team.

### Intervention

In the hospitals in the intervention condition, members of the specialized palliative care teams will receive a special training in the provision of proactive palliative care for patients with COPD. The training will be provided by academic palliative care professionals of the Radboudumc in Nijmegen. These trainings consist of two consecutive meetings of three hours each. The first meeting will take place in the month before start of the assessment. The second meeting will take place in the first month of the assessment. The following topics will be discussed:

● How to communicate end of life aspects with patient and family;

● How to create a patient-tailored proactive palliative care plan;

● How to anticipate on illness- and dying scenarios proactively;

● How to organize transfer of care to lung specialist and general practitioner (GP);

● How to perform a proactive palliative care plan in cooperation with the lung specialist.

During the controlled trial patients in the intervention condition who are assigned for proactive palliative care will meet with a member of the specialized palliative care team within one week after enrollment and at least monthly thereafter in the outpatients setting for at least one year or until death. The main informal caregiver of the patient will be asked to be present at those meetings. Guidelines for the proactive palliative care meetings in the ambulatory setting are adapted from the general guidelines palliative care in the Netherlands [35].

### Study parameters

#### Outcome measures indicator study

1. Primary outcome measures:

a. Length of time from the moment that a patient hospitalized for AECOPD meets two or more criteria of the set of indicators to death for any cause.

2. Secondary outcome measures:

a. Length of time from the moment that a patient hospitalized for AECOPD meets two or more criteria of the set of indicators to the first unexpected readmission to the hospital for AECOPD.

b. The sensitivity and specificity of the set of indicators, that indicate the start of proactive palliative care for patients hospitalized for COPD, in predicting death for any cause within 1 year.

c. The sensitivity and specificity of the set of indicators, that indicate the start of proactive palliative care for patients with COPD, in predicting the first unexpected readmission to hospital for AECOPD within 8 weeks.

d. Length of time from the moment that a patient hospitalized for AECOPD meets two or more criteria of the set of indicators to death as a result of pulmonary insufficiency.

e. The sensitivity and specificity of the set of indicators, that indicate the start of proactive palliative care for patients hospitalized for COPD, in predicting death as a result of pulmonary insufficiency within 1 year.

f. The contribution of individual indicators (or clusters), in predicting death for any cause within 1 year.

g. The contribution of individual indicators (or clusters), in predicting the first unexpected readmission to hospital for AECOPD within 8 weeks.

h. The contribution of individual indicators (or clusters), in predicting death as a result of pulmonary insufficiency within 1 year.

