#### Post-test assessment

A post-test assessment will be performed in all participating hospitals. The medical files of all participating patients will be examined retrospectively regarding the assessment period on the following measures:

● Number and length of hospitalization of unexpected hospital admissions for AECOPD

● Number and length of hospitalization of unexpected ICU admissions for AECOPD

● Are the choices of Advance Care Planning (ACP) documented in the medical file? (when yes/when no)

● Place of death (ICU/hospital/hospice/nursing/home/at home)

● Is preferred place of death known? (when yes/when no)

● Has this wish come true? (when yes/when no)

● Length of survival after meeting conditions for proactive palliative care

● The primary and secondary measures of the indicator study

In order to take account of possible confounding variables, other parameters are: age, gender, marital status, type of admission, (acute or planned), condition of living (single, or living together), place of living (home, residential home, or nursing home), Gold stage, comorbidities, and date of diagnosis.

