### Statistical analysis

#### Study parameter(s) indicator study

Non-continuous data will be reported as frequencies. Continuous variables normally distributed will be reported as mean ± standard deviation (SD). Not normally distributed data will be reported as median (interquartile range, IQR). The analytical plan consists of two steps. The first step will be to explore the discriminating power of meeting two or more criteria of the set of indicators for predicting death within one year and predicting unexpected hospital admission, respectively. The sensitivity and specificity for both death within one year and for unexpected admission to hospital will be presented. The second step will be to explore the discriminating power of individual indicators (or clusters) in predicting death within one year or unexpected admission to hospital. Univariable and multivariable logistic regression will be performed to examine which variables or cluster of variables are associated with death within one year (unexpected admission to hospital respectively). Variables will be eliminated one by one from the model based on likelihood ratio tests. Variables are eligible for inclusion into the final model if they are significantly associated with death within one year (unexpected admission to hospital respectively), with a p-value of < 0.10.

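### The indicator study's primary outcome starts only when a patient has two or more indicators, so it does not match its objective (discrimination) or the analysis described

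*Protocol article*

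**What the plan says.** All references are to the protocol article.

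- **Objective.** *Objectives indicator study*: "The primary objective is to assess the discriminating power of a set of indicators" for starting proactive palliative care.
- **Primary outcome, detailed definition.** *Outcome measures indicator study*, item 1a, has the interval run "from the moment that a patient hospitalized for AECOPD meets two or more criteria of the set of indicators to death for any cause". Secondary outcomes 2a (first unexpected readmission) and 2d (death from pulmonary insufficiency) start at the same moment.
- **Post-test data list.** *Post-test assessment* uses a similar anchor: "Length of survival after meeting conditions for proactive palliative care".
- **Primary outcome, short form.** *Study design*: "The primary outcome measure of the indicator study is time to death for any cause". The abstract says the same. Neither gives a restriction or a starting point.
- **Measures of discrimination.** Sensitivity and specificity appear as secondary outcomes 2b, 2c and 2e. Outcome 2b concerns the set's performance "in predicting death for any cause within 1 year".
- **Analysis.** *Statistical analysis*, indicator study: "The analytical plan consists of two steps". The first is to "explore the discriminating power of meeting two or more criteria of the set of indicators for predicting death within one year", and likewise unexpected admission, reported as sensitivity and specificity. For the second: "Univariable and multivariable logistic regression will be performed to examine which variables or cluster of variables are associated with death within one year", and again unexpected admission.
- **Survival methods.** Kaplan-Meier and Cox appear only under the intervention study. Survival there runs from enrollment, and the Cox model estimates the effect of palliative care.

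**The concern.** Discrimination is a contrast: patients who meet the rule against patients who do not. A time that starts when the rule is met exists on one side of that contrast only. Taken literally, the primary outcome gives a survival curve for qualifying patients and nothing to compare it with.

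The analysis section does make the contrast, but on binary outcomes that the outcome list ranks as secondary. The primary outcome is therefore detached both from the objective it should serve and from the analysis described. What is at stake is which result counts as the indicator study's main finding. As written, the designated primary outcome does not address the question, and the measure that does address it lacks primary status.

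The starting moment is also loosely fixed for qualifying patients. Some indicators in Table 1 predate the admission (age, earlier admissions, FEV1 before the exacerbation), while others refer to discharge or afterwards. The check for two or more criteria is made only in intervention hospitals, although the indicator values are recorded in both conditions.

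**Working it through.** **1. Who has a value of each outcome, and is it analysed?** The plan gives no figure to reproduce here, so the passages are set side by side.

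| Item | Starting point | Value if 0–1 indicators? | Used in the two-step analysis? |
|---|---|---|---|
| Primary outcome, item 1a | meeting two or more criteria | no | no |
| Secondary 2a, 2d | meeting two or more criteria | no | no |
| Time to death, abstract and *Study design* | not stated | yes, once a starting point is set | no |
| Secondary 2b: sensitivity and specificity, one-year death | one-year window | yes | yes, step 1 |
| Secondary 2f: individual indicators, one-year death | one-year window | yes | yes, step 2 |

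The version of the primary outcome with a stated starting point excludes the comparison group. The version that could include that group has no starting point. Neither is analysed.

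**2. Can survival in qualifying patients alone determine discrimination?** Let *q* be the share with two or more indicators, *a* one-year mortality among them, and *b* one-year mortality among the rest. Then

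- sensitivity = *qa* / [*qa* + (1−*q*)*b*]
- specificity = (1−*q*)(1−*b*) / [(1−*q*)(1−*b*) + *q*(1−*a*)]

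The document gives none of these rates. The values below are assumptions for illustration, with *a* held at 0.30. For *q* = 0.70:

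- *b* = 0.05: sensitivity = 0.210 / (0.210 + 0.015) = 0.93; specificity = 0.285 / (0.285 + 0.490) = 0.37
- *b* = 0.15: sensitivity = 0.210 / (0.210 + 0.045) = 0.82; specificity = 0.255 / (0.255 + 0.490) = 0.34
- *b* = 0.30: sensitivity = 0.210 / (0.210 + 0.090) = 0.70; specificity = 0.210 / (0.210 + 0.490) = 0.30

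In the last row sensitivity and specificity sum to 1, which is no discrimination. As *b* goes from 0.05 to 0.30, the pair runs from 0.86/0.58 to 0.50/0.50 for *q* = 0.50, and from 0.98/0.13 to 0.90/0.10 for *q* = 0.90. The same mortality in qualifying patients fits some discrimination or none, because *b* is missing.

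**3. How many patients might lack a value?** *Sample size calculation* needs 29 qualifying patients per hospital and expects to include 60 to 90. There are six hospitals.

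- 60 included: 60 − 29 = 31 without a value; 31/60 = 52%; 6 × 31 = 186 of 360
- 90 included: 90 − 29 = 61 without a value; 61/90 = 68%; 6 × 61 = 366 of 540

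**4. Are the data for a comparison collected?** Yes. The case report form records every indicator in both conditions, and Table 2 lists death within one year, date of death and date of first unexpected readmission from the medical files.

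**The case against.** The strongest reply is that the study can meet its objective as planned. Step 1 of the analysis addresses discrimination directly, outcome 2b is prespecified, the *Background* hypothesis is framed as death within one year and readmission within eight weeks, and the data cover all participants. The abstract and *Study design* also carry no restriction to qualifying patients. All of this stands, and it limits the point to a mismatch.

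It also rules out four stronger readings that a reader might infer:

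- *That the primary objective cannot be answered.* It can, through outcome 2b.
- *That reporting sensitivity and specificity would switch the primary outcome after the fact.* These measures are prespecified, so reporting them follows the plan. Only their rank is at odds with the objective.
- *That the one-year binary analysis is a fault because it ignores timing.* With a fixed-window hypothesis and one year of follow-up it is a legitimate choice.
- *That more than half the patients are known to lack a primary outcome.* The 29 and the 60 to 90 are recruitment figures for the intervention study, not a stated prevalence. The indicators are broad (age over 70, one admission in the last year), so the true share may differ.

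A further reply is that a full analysis plan, not shown here, may name a survival method. That is fair, and the absence of such a method in an article would not be a finding alone. It does not remove the conflict in what the article states: two forms of the primary outcome, and a two-step plan that uses neither.

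**Conclusion.** The point holds as a mismatch between the primary outcome, the objective and the described analysis. Under item 1a, patients with 0–1 indicators have no value, so the outcome cannot by itself measure discriminating power. Outcomes 2a and 2d share the defect. The unrestricted wording elsewhere conflicts with item 1a, and the analysis rests on outcomes ranked as secondary.

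This conclusion follows from the text and needs no assumed rate. The sensitivity and specificity figures only illustrate why a comparison group is needed. The share without a value, 52% to 68%, applies only under the wording of item 1a and only if the planning figures reflect how many patients qualify. No data are lost.

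**What to change.** Reconcile *Outcome measures indicator study* and *Post-test assessment* with the abstract, *Study design* and *Statistical analysis*, in one of two ways:

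- **(a) Keep time to death as primary.** Define it, and outcomes 2a and 2d, for all included patients from one common origin, such as enrollment or the day of indicator assessment. Compare two or more with fewer than two indicators by Kaplan-Meier and a hazard ratio or C-statistic. State how the indicator on blood gases at discharge is handled when discharge falls after the chosen origin.
- **(b) Make sensitivity and specificity for one-year death (now 2b) primary.** This is the smaller change and matches the analysis already described. Outcomes 2a and 2d would still need a common origin.

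Under either option, stratify by condition or report control hospitals separately. Qualifying patients in intervention hospitals receive care that the protocol hypothesises will prolong survival, so a pooled estimate would mix prognosis with treatment.

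The cost is wording and slightly more analysis work. No new data are needed.
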